### Sample size

2.3

PASS was used for sample size determination. According to the previous study, WOMAC Function Score of KOA patients decreased by 12.1 points after acupuncture, by 9.4 points after sham acupuncture and 5.6 points after education, while WOMAC pain Score of KOA patients decreased by 3.6 points after acupuncture, by 2.6 points after sham acupuncture and 1.5 points after education.^[18]^ Based on the previous study and our clinical experience, we anticipated a reduction of WOMAC total score by 17 points after acupuncture with the *deqi* sensation, a reduction by 13 points after acupuncture without the *deqi* sensation and a reduction by 8 points in the wait-list control. With α = 0.05, 1 – β = 0.9, and a standard deviation of 10, we need at least 99 participants in total. Considering a dropout rate of 10%, a total of 108 participants will be included in this trial.

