### Primary outcome

4.1

We will use the Western Ontario and McMaster Universities Osteoarthritis Index (WOMAC) as the primary outcome measure.^[19]^ It consists of 24 items assessing the patients with KOA pain (5 items), stiffness (2 items) and physical function (17 items). The score ranges for the pain, stiffness and physical function subscales are, respectively, 0–50, 0–20 and 0–170, resulting in a total range of 0–240. Higher scores indicate more severe symptoms or physical disability. The evaluation will be performed at week 16 after randomization.

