### Statistical analysis

4.6

In this trial, we will implement the intention-to-treat analysis and per-protocol (PP) analysis. The intention-to-treat analysis will be used for all allocated participants in the baseline. This trial focuses on the long-term effect of acupuncture, and the observed data will be used as the primary analysis. Primary analysis will be based on intention-to-treat population, including participants with at least 1 assessment of the primary outcome and 1 acupuncture session. Per protocol (PP) analysis will be performed to test the robustness of the primary analysis. PP population will include participants receiving at least 12 sessions of acupuncture and be assessed at week 16.

The demographic and baseline characteristics among 3 groups will be compared using one-way analysis of variance (ANOVA). A χ^2^ test will be used for categorical variables. Due to the occurrence of self-healing tendency in KOA, it is important to testify the existence of the long-term effect of acupuncture effect. The clinical outcomes will be compared among the acupuncture with the *deqi* group, acupuncture without the *deqi* group and the waiting treatment group at every time points (week 0, 4th, 8th, 12th, 16th, 20th, and 24th after randomization) by using the repeated measures ANOVA (3 independent groups with repeated measures).

Clinical outcomes will be analyzed using SPSS 22.0 statistics software (IBM SPSS Statistics, IBM Corp, Somers, NY, USA). Data on Skewed distribution will be normalized. Means, standard deviations, and 95% confidence intervals (CIs) will be used to describe the continuous data. All statistical hypotheses are two-sided tests, and the significance test level α = 0.05, giving the test statistic and its corresponding *P* value, with *P* ≤ .05 as statistically significant. The data will be analyzed by statisticians who are blinded to the test settings. All confidence intervals will be two-sided 95% intervals among the 3 groups (group A, group B and group C).

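### The primary outcome is WOMAC at week 16, but the analysis section fixes neither the test nor the contrast that decides it; unadjusted pairwise tests there carry about 9% to 12% family-wise error

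*Protocol article*

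**What the plan says.** Protocol article, section 4.1 (Primary outcome), names WOMAC and gives one time for it: "The evaluation will be performed at week 16 after randomization". Section 4.2.1 lists WOMAC at weeks 0, 4, 8, 12, 20 and 24 as secondary.

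Section 4.6 (Statistical analysis) compares the clinical outcomes of the three groups "at every time points (week 0, 4th, 8th, 12th, 16th, 20th, and 24th after randomization") by repeated measures ANOVA. On the error level it says: "All statistical hypotheses are two-sided tests, and the significance test level α = 0.05". P values up to .05 are to be taken "as statistically significant". Week 16 appears in that section only in the visit list and in the definition of the per-protocol population. No effect of the model (group, group-by-time, or the week-16 comparison) and no pair of arms is named as decisive.

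Section 2.3 (Sample size) expects mean reductions in WOMAC total of 17, 13 and 8 points in the three arms and concludes: "With α = 0.05, 1 – β = 0.9, and a standard deviation of 10, we need at least 99 participants in total".

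**The concern.** The trial asks two questions: whether acupuncture has a lasting effect in knee osteoarthritis, and whether deqi contributes to it. The first rests on A against C and the second on A against B. A three-arm omnibus result answers neither by itself.

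The planned model does not supply the missing link. The overall group effect of a repeated measures ANOVA averages over all visits entered, here including baseline and the end of treatment at week 4. The group-by-time effect tests whether the profiles differ in shape. Neither is the week-16 comparison that section 4.1 calls primary.

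So the analyst must choose the decisive effect and contrasts, and the only rule stated is an unadjusted 0.05 for each hypothesis. At stake is whether the nominal 5% applies to the trial's main conclusions.

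**Working it through.** **1. The plan's own figure.** Inputs from section 2.3: mean reductions 17, 13 and 8; SD 10; alpha 0.05; power 0.90. Allocation is 1:1:1 (section 2.4).

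- Grand mean = (17 + 13 + 8)/3 = 12.667.
- Deviations are 4.333, 0.333 and -4.667. Their squares sum to 18.78 + 0.11 + 21.78 = 40.67.
- Effect size f = sqrt(40.67/3)/10 = 3.682/10 = 0.368.
- One-way three-group F test (noncentral F): power is 0.899 with 32 per arm (96) and 0.908 with 33 per arm (99).

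The stated 99 is therefore the smallest balanced total that reaches 0.90 for a single omnibus test of WOMAC total. The design calculation matches one three-arm test, not a set of pairwise tests.

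**2. Error rate at week 16 alone.** Simulation under no effect: 33 per arm, normal data, 20,000 replicates, variance pooled over the three arms (3 × 33 - 3 = 96 degrees of freedom), two-sided 0.05 per test.

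| Tests at week 16 | Chance of at least one false positive | If the tests were independent |
|---|---|---|
| Omnibus F test | 4.9% | 5% |
| One named contrast (A-B) | 5.0% | 5% |
| A-B and A-C | 8.7% | 1 - 0.95² = 9.75% |
| All three pairs | 11.8% | 1 - 0.95³ = 14.3% |
| Pairs tested only if the omnibus is significant | 4.9% | not applicable |

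The simulated values lie below the independence values because the contrasts share arms.

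**3. What the repeated measures ANOVA gives.** Its overall group effect is one 5% test. If group and group-by-time were both read at 0.05, the bound is 0.05 + 0.05 = 10%. Neither effect isolates week 16.

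**4. Error rate if any follow-up visit could decide.** Treatment ends at week 4, which leaves five post-treatment visits (8, 12, 16, 20, 24). The document gives no between-visit correlation, so a common correlation r is assumed and varied.

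| Any of five visits | r = 0 | r = 0.5 | r = 0.9 |
|---|---|---|---|
| Omnibus F at each visit | 22.9% | 18.2% | 10.4% |
| Three pairs at each visit | 48.0% | 38.5% | 23.1% |

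These figures describe a decision rule that the document does not state. They show only what would follow if it were used.

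**5. Why an omnibus gate is enough with three arms.** If any two of the pairwise null hypotheses are true, all three means are equal, so every intersection of pairwise nulls is the global null. Testing the global null at 0.05 and then each pair at 0.05 is therefore a closed procedure. It holds the family-wise error at 5% under the global null. When only one arm differs, it also holds 5%, because only one pairwise null is still true (checked by simulation for A-B when only C differs: about 5%).

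**The case against.** A reader might infer that the plan singles out nothing as confirmatory, and that the chance of a false long-term claim is therefore some 17% to 50%. The documents do not support that.

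- Section 4.1 fixes the outcome and the week, and section 4.2.1 makes the other WOMAC visits secondary. Section 4.6 ties the per-protocol check to assessment at week 16.
- No section says that one significant visit or pair establishes the effect. A common 0.05 for reporting is not a success criterion.
- The planned test is a repeated measures ANOVA, not separate tests at each visit. The visit list, which includes week 0, may simply describe the repeated factor.
- The 17% and the 50% come from two different procedures at two different assumed correlations (omnibus at 0.7, three pairs at 0.3), and both count week 4, which is not follow-up. Over r = 0 to 0.9 with six visits, the same calculations run from about 11% to 54%.
- The sample size reproduces as one omnibus test. At week 16, that test alone has 5% error.

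All of this stands, and it removes the large figures. It is also fair that post-hoc methods and test order are often left to an analysis plan. That does not dispose of the point, because section 4.6 does not stay silent: it states one unadjusted level for all hypotheses and describes a model whose effects are not the primary comparison named in section 4.1. The mismatch lies within the article.

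**Conclusion.** The point holds in a limited form. The outcome and the time are fixed; the deciding test and contrast are not. If the contrasts needed for the acupuncture and deqi claims are tested at week 16 under the stated rule, the family-wise error is about 9% (A-B and A-C) to 12% (all three pairs). It is 5% if a single omnibus test or one named contrast at week 16 decides.

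The 9% and 12% assume 33 per arm, normal data with equal variances, and ungated pairwise tests; they need no assumption about between-visit correlation. The wider range of about 10% to 48% over the five post-treatment visits depends on the test used, on an assumed correlation from 0.9 down to 0, and on an any-visit rule that the article does not contain. It should not be quoted as the trial's error rate.

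**What to change.** In section 4.6, state that:

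1. The confirmatory analysis is the three-arm comparison of WOMAC total at week 16, at two-sided 0.05.
2. A-C, A-B and B-C at week 16 are each tested at 0.05 only if that comparison is significant.
3. WOMAC at other visits and all other scales are secondary or supportive, reported as differences with 95% confidence intervals.

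This matches the omnibus test that reproduces the 99 participants, and it lowers the alpha of no pairwise test. The cost is a few sentences and fewer results that may be presented as confirmatory. Data collection and sample size are unaffected. The gate does not add power for single pairs: on the plan's own assumptions with 33 per arm, unadjusted power is about 37% for A-B, 53% for B-C and 96% for A-C, so a non-significant A-B result should be read with its interval.

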## Discussion

5

According to the characteristics of KOA pain, it is a category of “knee cramps”. Chronic pain is a common clinical symptom of KOA, which directly leads to the decrease of functional activities and quality of life.^[2]^ The main treatment goals of KOA are to relieve or eliminate pain, improve joint function, prevent and delay the progression of the disease, and improve the quality of life of patients,^[27]^ but there is no good treatments currently. As a representative of traditional Chinese medicine, acupuncture has a remarkable curative effect on KOA,^[28,29]^ and the long-term effect of acupuncture which is an important feature of acupuncture analgesia has been confirmed in many clinical trials.^[30–34]^ However, KOA is a chronic joint disease, and the long-term effect is very important for the evaluation of the treatment of acupuncture on KOA, but whether there is a long-term effect on KOA requires further studies.

“The quicker the *qi* arrives, the faster the acupuncture effect acquires” (“*Biao You Fu*,” a Poetic Prose on the Elucidation of Acupuncture). *Deqi* is not only the key to acupuncture treatment, but also a good entry point to study the effect of acupuncture on the long-term analgesia effect of KOA. Modern clinical trials have considered that *deqi* plays an essential role in the process of achieving the acupuncture effect.^[26,35–37]^ For example, Xiong et al^[35]^ found that in the treatment of primary dysmenorrhea by acupuncture, the pain level of the *deqi* group was significantly improved after acupuncture treatment, which led them to conclude that *deqi* plays a decisive role in the therapeutic effect of acupuncture. In a systematic review of chronic pain in the knee, Wu WF et al^[36]^ found that acupuncture at *Quch*i Point (LI11) for the treatment of primary high acupoint pressure showed that the antihypertensive effect of the non-*deqi* group was significantly lower than that of the *deqi* group.

The long-term effect of acupuncture which is an important feature of acupuncture treatment after cessation^[38]^ refers to the acupuncture effect that persists after the end of acupuncture treatment. Compared with immediate effect, the long-term effect is stronger, wider, more lasting and can be accumulated.^[39]^ Many studies have shown that the long-term effect is an important part of acupuncture that is different from placebo effect, and it is an important focus for improving the efficacy of acupuncture. It has been recorded in a lot of ancient Chinese medical books and reported in many kinds of clinical and animal trials. For example, acupuncture treatment for chronic tension-type headache,^[13]^ migraine,^[14]^ primary insomnia,^[15]^ tinnitus,^[16]^ chronic knee pain,^[40]^ rats with cerebral ischemia and reperfusion,^[41]^ etc. These studies have confirmed that the long-term effect is an important feature of acupuncture analgesia. However, the long-term effect is not clear about the efficacy of KOA. Therefore, in order to demonstrate the effectiveness of the *deqi* sensation on the long-term acupuncture effect in patients with knee osteoarthritis, we design a randomized controlled trial with a treatment period of 4 weeks and an observation period of 20 weeks to investigate and evaluate the long-term effect of acupuncture for KOA.

The randomized controlled study design is an in-depth study of reliable methods based on the long-term analgesic effect of acupuncture. At the same time, it is a randomized controlled study that is an important source of high-quality evidence-based medical evidence for acupuncture. In the trial, we take acupuncture without *deqi* group as the control group. It is often regarded as a sham control group, because its acupuncture depth is only broken and does not reach the anatomical layer of the acupuncture point. Studies^[42–44]^ have shown that the placebo effect of sham acupuncture is more pronounced than drug-based placebo, especially for subjective outcomes and pain management. Therefore, our study has set a sham acupuncture group to eliminate the effects of placebo effects and patients’ expectations. And in the idea of acupuncture treatment of knee osteoarthritis, local acupoints have been used since ancient times. “*Su Wen*” says, local *Ashi* Point for the treatment of knee pain. A number of modern clinical studies^[44,45]^ have shown that local acupoints are widely used in the treatment of KOA by acupuncture, and the curative effect is remarkable. Some researchers^[45]^ used data mining to analyze the relevant literature of modern acupuncture treatment for KOA, and found that *Dubi*, *Neixiyan* and *Yanglingquan* were the top 3 acupoints with the high frequency. Another study^[46]^ shows that *Ashi* point is also one of the high-frequency acupoints. Thus, this study will select *Dubi*, *Neixiyan* and *Yanglingquan*, *Yinlingquan* as the acupuncture points. At the same time, depending on the patient's condition, 2 local acupuncture points can be added.

In order to improve the reliability of the study data, we carry out quality control from the following aspects:

1.Recruitment of middle-aged and elderly patients with mild to moderate recurrent knee pain in the past month to avoid the impact of other diseases on pain assessment;2.In order to alleviate patients doubts about different interventions, patients in each group will be treated in different rooms, and patients in each group will be forbidden to talk.3.The acupuncturist is a doctor with more than 6 years of work experience and a medical practitioner certificate. Relevant personnel and data evaluators responsible for recruiting patients are required to undergo rigorous training before the study to ensure that all experimental procedures have uniform standards and avoid observational bias.4.Emotion monitoring. During the whole study, not only the emotional changes of patients will be evaluated on time by the emotion monitoring scales, but also the emotional changes of each patient should be paid close attention in order to eliminate the influence of emotional changes on the disease.

Of course, this study also has some shortcomings, mainly reflected in the following 2 aspects:

1.Because this study has a long observation period, it will result in a higher rate of abscission, which will affect the results of the study. Therefore, we should maintain a good doctor-patient relationship with patients during the study, and the part of the scales involved in this study are self-rating scale, which can be carried out subjectively by patients to better improve the quality of studys data;2.The patients enrolled in this study are limited to mild to moderate KOA patients, so the results of this study have some limitations, they may only be applicable to mild to moderate KOA individuals.

Most domestic and international medical treatment guidelines recommend acupuncture for knee osteoarthritis, but the long-term effect of acupuncture for KOA is not fully defined. Therefore, this study designs a clinical study with a treatment period of 4 weeks and a follow-up period of 20 weeks, aiming to study the long-term effect of acupuncture and the influence of the *deqi* sensation on the long-term in the treatment of KOA, and to provide a clinical basis for treatment of patients with mild to moderate knee osteoarthritis in clinic.

## Trial status

6

Protocol version number V1.0, January 21, 2020. The trial is currently in the participant recruitment stage. The trial began recruitment on March 1, 2020 and is expected to complete on December 31, 2021.
